# Quality assurance

Appropriate quality assurance measurements will be undertaken:

- Collection and use of data is only possible after formal written consent from the participants (or their representatives).
- Participants will be provided with information related to the study (see appendix 2 ICF) and will have the possibility to opt-out at any moment (see appendix 2 ICF).
- Data will be handled and managed confidential and encoded using REDCAP – all as stated in section 12 below.

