### 3.4 Trial Design

single-centre pre-post implementation study on the traumatology ward of the University Hospitals Leuven

**Usual care (pre-cohort):** the control group receives usual care on the traumato ward. This means that the patient is cared for by a surgical resident. The interprofessional team furthermore consists of ward nurses, a physiotherapist, an occupational therapist and a social worker. No tailored geriatric protocols are available to the traumato team, except for those that are available hospital-wide for all patients (e.g. fall prevention, delirium). Geriatric expertise is available upon active request by the traumato team and includes the comprehensive evaluation of the patient by a geriatric nurse (consultation model).

Due to the design of the G-COMAN strategic project and its predefined strict timing schedule (a phased implementation with the need of a rapidly full implementation), the timeframe for inclusion of the pre-cohort is limited. At the end of the pre-cohort, the predefined sample size will not be reached. To obtain sufficient included patients in the pre-cohort, this patient cohort will be supplemented with patients of which retrospectively information will be gathered. This results in a pre-cohort that will be partly prospective and partly retrospective.

**Geriatric co-management intervention, quality-improvement project G-COMAN (post-cohort):** A dedicated traumato nurse (G-COMAN nurse) will systematically perform a frailty screening in all newly admitted older patients on the traumato ward to evaluate if they are to be included in the G-COMAN program. In eligible patients, a comprehensive geriatric assessment (CGA) will be performed by the G-COMAN nurse. Based on identified potential problems, a tailored care plan based on predefined geriatric protocols will be launched. As part of the project a geriatric specialist nurse will provide every weekday training and education of the G-COMAN nurse and other team members on the traumato ward. The implementation of automated care plans and predefined geriatric protocols will be coordinated by a G-COMAN project coordinator, as well as the organisation of focus groups and intervisions to ensure smooth and supported collaboration.

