# Selection and withdrawal of subjects

### 4.1 Inclusion criteria

Patients:

- 75 years of age or older

- male or female

- admitted to the traumatology ward (E456) with an osteoporotic fracture

- Proximal femoral fracture
- Proximal humeral fracture
- Fracture of the pelvis / acetabulum
- Fracture of the thoracic/lumbar vertebrae (multiple fractures are allowed)
- Fracture of the wrist

- ability of the patient or assigned representative to understand the content of the patient informed consent form (see **appendix 2** for the pre-post cohort and **appendix 2.1** for the feasibility study).

- signed and dated informed consent.

Health care professionals:

- Working on E456

- Had four or more weeks of ‘full time’ experience with the program.

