### 4.2 Exclusion criteria

- patient in palliative care setting not expected to live longer than 3 months.

- multi-trauma injuries except for presence of multiple vertebral fractures

- patient or assigned representative are unable to speak and/or understand Dutch

- periprosthetic fracture

- concomitant joint-infection

- admission from another hospital or hospital unit (reason: no full baseline data on premorbid conditions such as mobility, functional status, … available)

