### 12 months after admission

**Mortality** will be checked in the electronic patient record (KWS) which is linked the Federale Kruispuntbank and survival status will be double checked with patients/ care givers via questionnaire. **Quality of life** (EQ-5D) and **residential status** will also be checked in the questionnaire. Also the **presence of new falls and fractures** will be asked as well as use of calcium/vitamin D and anti-osteoporosis **medication** in a questionnaire. Only mortality will be retrospectively collected.

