# Ethics and regulatory approvals

| The trial will be conducted in compliance with the principles of the Declaration of Helsinki (current version), the principles of GCP and in accordance with all applicable regulatory requirements. This protocol and related documents will be submitted for review to Ethics Committee and to the Federal Agency for medicinal products for Clinical Trial Authorisation.  The Study can and will be conducted only on the basis of prior informed consent by the Subjects, or their legal representatives, to participate in the Study. The Participating Site shall obtain a signed informed consent form (ICF) for all patients prior to their enrollment and participation in the Study in compliance with all applicable laws, regulations and the approval of the (local) Ethics Committee, if required. The Participating Site shall retain such ICFs in accordance with the requirements of all applicable regulatory agencies and laws.  The Investigator and the Participating Site shall treat all information and data relating to the Study disclosed to Participating Site and/or Investigator in this Study as confidential and shall not disclose such information to any third parties or use such information for any purpose other than the performance of the Study. The collection, processing and disclosure of personal data, such as patient health and medical information is subject to compliance with applicable personal data protection and the processing of personal data (Regulation (EU) 2016/679 also referred as the General Data Protection Regulation ("GDPR") and the Belgian Law of July 30 2018 on the protection of natural persons with regard to the processing of personal data).  Data are **coded**; there continues to be a link between the data and the individual who provided it. The research team is obligated to protect the data from disclosure outside the research according to the terms of the research protocol and the informed consent document. The subject’s name or other identifiers should be stored separately from their research data and replaced with a unique code to create a new identity for the subject. Note that coded data are not anonymous. |
| --- |

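### Signed consent is required of every patient without exception, yet the pre-cohort alone is topped up retrospectively; the protocol does not reconcile the two, and either reading selects the control group differently from the post-cohort.

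*Protocol*

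**What the plan says.** Consent is stated as a universal condition in three places:

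- Section 4.1 lists "signed and dated informed consent" among the inclusion criteria for patients.
- Quality assurance: "Collection and use of data is only possible after formal written consent from the participants (or their representatives".
- Ethics and regulatory approvals: the site "shall obtain a signed informed consent form (ICF) for all patients prior to their enrollment and participation".

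The last two allow a representative to act for the patient. None of the three treats retrospective cases separately.

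Section 3.4 says of the prospective pre-cohort recruitment that "At the end of the pre-cohort, the predefined sample size will not be reached", and that "this patient cohort will be supplemented with patients of which retrospectively information will be gathered". The post-cohort has no such supplement. The number of retrospective patients, their calendar window and the way they are sampled are not stated; section 4.3 gives dates only for the prospective periods.

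The table in section 3.6 marks complications, length of stay, unplanned readmissions and mortality as available for the retrospective pre-cohort. Section 5.1 agrees: mortality is among the discharge items that can be collected retrospectively, mortality and readmission are collected at 1 month, and for the 12-month assessment "Only mortality will be retrospectively collected".

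**The concern.** Patients in the prospective pre-cohort and the post-cohort are asked for consent before enrolment, with most of their outcome still ahead. Retrospective patients have already been treated, so consent could be sought only once some or all of the outcome has happened. A consent rule that is harmless in the prospective cohorts can therefore select on the outcome itself in the retrospective part, and that part lies entirely in the control group.

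The primary endpoint (in-hospital complications) and several secondary endpoints, mortality among them, are compared between the cohorts. The covariates in section 8.2 describe pre-fracture status; adjusting for them does not undo selection on survival or on having a relative who answers. Section 8.2 names lack of randomisation, death and loss to follow-up as sources of bias, but not this mechanism.

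**Working it through.** **1. The two readings side by side**

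- *Rule applied literally.* A retrospective control needs a signature from the patient or a representative before any data are used. Patients who died, cannot be traced or have no willing representative may be missing. Usual care then looks healthier, to the programme's disadvantage.
- *Rule not applied.* Retrospective controls are taken from records whether or not they would have consented, against the text of 4.1, Quality assurance and Ethics. Unselected controls are then compared with consenting post-cohort patients. If non-consenters fare worse, this favours the programme.

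**2. Inputs**

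From section 8.1: 108 per group, 5% loss, a 20-point reduction, usual-care complication rates of 55% to 71%. The 108 can be reproduced: 71% vs 51%, two-sided 0.05, power 0.80, with continuity correction gives 102, and 102/0.95 = 107.4, rounded up to 108. About 102 per group are therefore evaluable.

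Not in the documents, so assumed: retrospective share of controls *f*; share of retrospective patients missed *d*; event rates overall and among those missed.

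**3. Mortality at 12 months, literal reading**

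Let *m* be true mortality, and let those missed all be dead before approach.

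- Retrospective part: (m − d)/(1 − d)
- All controls: (1 − f)·m + f·(m − d)/(1 − d)

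With m = 0.25, d = 0.10, f = 0.5:

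- (0.25 − 0.10)/0.90 = 0.167
- 0.5 × 0.25 + 0.5 × 0.167 = 0.208

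Control mortality reads 20.8% instead of 25%, 4.2 points lower, with no treatment effect.

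The ceiling sets retrospective mortality to zero, so controls read (1 − f)·m. The relative understatement is then *f* itself: 25% if f = 0.25, 50% if f = 0.5. It requires all consent to be sought after month 12 and no representative ever to sign.

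**4. Primary endpoint, literal reading**

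Assume a true control rate p = 0.60, a post-cohort rate of 0.40 and complication rate *c* among those missed.

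- Retrospective part: s = (p − d·c)/(1 − d)
- All controls: (1 − f)·p + f·s

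Power is the normal-approximation power for two proportions with 102 per group; without selection it is 82%.

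| f | d | c | s | Control rate | Shift (points) | Power |
|---|---|---|---|---|---|---|
| 0.25 | 0.05 | 0.70 | 0.595 | 0.599 | −0.1 | 81.5% |
| 0.50 | 0.10 | 0.80 | 0.578 | 0.589 | −1.1 | 77% |
| 0.75 | 0.30 | 0.90 | 0.471 | 0.504 | −9.6 | 32% |

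The first and last rows are the extremes of the grid f = 0.25 to 0.75, d = 0.05 to 0.30, c = 0.70 to 0.90.

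**5. The other reading**

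Suppose a share *d* of eligible patients in the prospective cohorts does not consent, with complication rate *c*. Consenters then have rate *s*. With no programme effect, controls read (1 − f)·s + f·p and the post-cohort reads s, a difference of f·(p − s). At f = 0.5, d = 0.10, c = 0.80 this is 0.5 × (0.600 − 0.578) = 0.011, or 1.1 points in the programme's favour. On the same assumptions the size matches the middle row of the table, with the opposite sign.

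**The case against.** A reader might infer that deceased and unreachable patients drop out of the control group. The protocol does not say so, and its plan points the other way: collecting in-hospital, 1-month and 12-month mortality retrospectively makes sense only if deceased patients are meant to be included. Representatives may consent, which would reduce any loss by an unknown amount. The consent-form appendices are not available here, so a retrospective consent route may exist outside the visible text. Under the literal reading the bias runs against the programme and would not manufacture a benefit, and in the middle case the primary endpoint moves by only about one point.

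A reader might also infer that control mortality is understated by 25% to 50%. That range is the assumed retrospective share restated; it ignores representatives and deaths after consent.

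The exclusion in 4.2, "patient in palliative care setting not expected to live longer than 3 months", might be thought to be applied with hindsight to past cases. Nothing in the documents shows this; it concerns a care setting that may well be on record at admission.

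These points remove any claim to a known direction or a large effect. They do not remove the contradiction. The intention to include deceased patients sits beside a rule that forbids using their data without a signature, and the visible text does not say whether a representative may sign after death. Nor is this a matter to leave to the statistical analysis plan: consent, eligibility and the sampling frame belong in the protocol. Only the sensitivity analysis could reasonably sit there.

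**Conclusion.** The concern holds as an unreconciled contradiction between 3.4 on one side and 4.1, Quality assurance and Ethics and regulatory approvals on the other. As written, the retrospective part of the control group cannot be assembled without either breaching the consent rule or risking selection on survival, reachability or representation. Both routes select controls differently from the post-cohort, in opposite directions.

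The size cannot be bounded from the documents, because the retrospective share, the timing of consent and the number of patients missed are all unstated. On assumed inputs, the control complication rate shifts by anything from 0.1 to 9.6 points under the literal reading, about 1 point in the middle case, and 12-month control mortality by about 4 points in a moderate case. These are illustrations, not estimates.

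**What to change.** - Amend 3.4, 4.1, Quality assurance and Ethics and regulatory approvals so that they agree. Define the retrospective part as all consecutive admissions in a fixed calendar window that meet the other criteria of 4.1 and 4.2, deceased patients included, under a waiver or opt-out approved by the ethics committee.
- As a precaution, judge the 4.2 criteria for these cases from notes dated at admission.
- From the screening log already planned in 5.1, report by cohort the numbers screened, eligible, deceased, unreachable, refusing and included.
- Add a sensitivity analysis restricted to prospective controls, for complications and mortality.

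The first step removes the contradiction and the survival selection, but leaves unselected retrospective controls beside consenting prospective patients. The counts and the sensitivity analysis are there to show how much that matters.

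The cost is a protocol amendment and an ethics request, with no extra patients or visits. The sensitivity analysis will be less precise, since it uses only part of the control group.

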# Direct access to source data and documents

The investigator(s) and the institution(s) will permit trial-related monitoring, audits, EC review, and regulatory inspections (where appropriate) by providing direct access to source data and other documents (ie patients’ case sheets, blood test reports, X-ray reports, histology reports etc).

# Ethics and regulatory approvals

| The trial will be conducted in compliance with the principles of the Declaration of Helsinki (current version), the principles of GCP and in accordance with all applicable regulatory requirements. This protocol and related documents will be submitted for review to Ethics Committee and to the Federal Agency for medicinal products for Clinical Trial Authorisation.  The Study can and will be conducted only on the basis of prior informed consent by the Subjects, or their legal representatives, to participate in the Study. The Participating Site shall obtain a signed informed consent form (ICF) for all patients prior to their enrollment and participation in the Study in compliance with all applicable laws, regulations and the approval of the (local) Ethics Committee, if required. The Participating Site shall retain such ICFs in accordance with the requirements of all applicable regulatory agencies and laws.  The Investigator and the Participating Site shall treat all information and data relating to the Study disclosed to Participating Site and/or Investigator in this Study as confidential and shall not disclose such information to any third parties or use such information for any purpose other than the performance of the Study. The collection, processing and disclosure of personal data, such as patient health and medical information is subject to compliance with applicable personal data protection and the processing of personal data (Regulation (EU) 2016/679 also referred as the General Data Protection Regulation ("GDPR") and the Belgian Law of July 30 2018 on the protection of natural persons with regard to the processing of personal data).  Data are **coded**; there continues to be a link between the data and the individual who provided it. The research team is obligated to protect the data from disclosure outside the research according to the terms of the research protocol and the informed consent document. The subject’s name or other identifiers should be stored separately from their research data and replaced with a unique code to create a new identity for the subject. Note that coded data are not anonymous. |
| --- |

# Data Handling and Data Management

Study data will be collected and managed using REDCap®, a secured web application for building and managing electronic surveys and databases. The data will be encoded. Every patient will receive a unique study number and there will be no combination of elements on the data collection forms that allows identification of the individual. Only the principal investigator (MD), the subinvestigator (JF) and the research assistant (SJ) will be able to link the data collected in REDCap® to the patients’ electronic medical record using a subject identification log. The document will be stored separately and in a safe location by the principal investigator (MD) for 10 years, afterwards it will be deleted. The research assistant (x) will introduce the data in REDCap®. The principal investigator (MD) will check correct data collection. Data analysis in the framework of this study will be performed in collaboration with the Leuven Biostatistics and Statistical Bioinformatics Centre. Data collected in this study can be shared with researchers involved in this study upon their request to perform sub analyses. All are affiliated with UZ or KU Leuven. The study does not involve external parties.

# Translational research

No biological material will be collected/shipped/stored/used for the study.

# Publication Policy

Publications will be coordinated by the Investigators. Authorship to publications will be determined in accordance with the requirements published by the International Committee of Medical Journal Editors and in accordance with the requirements of the respective medical journal. The results of the study will be submitted by the core research team as conference abstracts and as publications in professional journals and international peer-reviewed journals.

# Insurance/Indemnity

In accordance with the Belgian Law relating to experiments on human persons dated May 7, 2004, Sponsor shall assume, even without fault, the responsibility of any damages incurred by a Study Patient and linked directly or indirectly to the participation to the Study, and shall provide compensation therefore through its insurance.”

Due to the nature and design of the study (observational study) the risks for patients are considered minimal. Hence, the regular insurance policy of UZ Leuven – KU Leuven is applicable.

# Financial Aspects

Multiple funding options as King Baudoin Foundation (Funds De Lava-Schneider), C2 and FWO predoctoral fellowship will be explored this year (2021) and in the following year.

Meanwhile the PhD student will be employed by the Department of Public Health and Primary Care, Division Gerontology and Geriatrics, KU Leuven.

